#### Baseline randomization (day −1 or 0)

Eligible subjects will be assessed by our registered CMPs via telemedicine in this trial, during which medical history and concomitant medication will be recorded. After stratification, subjects will be randomly assigned in a 1:1 ratio to receive up to 14 days of either modified Yinqiao Powder-Maxing Ganshi Decoction (about 33.4–59.7 g each day) or placebo granules (about 33.4–59.7 g each day). Specifically, the stratified randomisation is based on age (A: “18–49 years old” and B: “50–65 years old”) and the number of vaccination (a: “received 3 or more doses - fulfilling government vaccination requirement” and b: “received 2 doses or less of vaccine - yet to be fully vaccinated”). Subjects will be divided into two groups by age: one group is “18–49 years old” and the other one is “50–65 years old”; then they will be further divided into two groups within the different age group by the numbers of vaccination: one group is “received 3 or more doses of vaccine, and the another is “received 2 doses or less of vaccine”. Four subgroups will be created after stratification and subjects in each subgroup will be randomly assigned to either the treatment or placebo group. The distribution of age and number of vaccinations between the two groups will be roughly comparable after stratified randomisation. The IMP will be prescribed by Registered CMPs and will be sent to patients by delivery service. The current Western medicine treatment can continue during the study period.

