### Sample size and statistical methods

#### Sample size estimation

The primary outcome of the study is the time between starting medication and body temperature returning to normal, i.e., the time to fever resolution after the first treatment. Based on previous studies, we assumed the standard deviation (SD) is 0.7, and the time to fever resolution of half a day (0.5 days) would have clinical significance (Qiu et al., 2020; Chen et al., 2021). Therefore, to detect such a difference between groups, 38 in each group will be needed with a power of 80% and a 5% 2-tail significance level. To allow for possible dropouts during the study period, we inflate this value by 20%, hence a total of 96 patients will be needed for the proposed study and 48 in each group (12 in each sub-group).

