#### Randomization and blinding

A random number table will be generated with a computerized random number generator program. The random allocations will be put into opaque envelopes with sequential study numbers by an independent researcher. Two sets of the envelope will be prepared, one set will be for randomization at the site and another set stored in the investigator’s office for emergency unblinding. Each subject will be assigned with a sequential study number and the corresponding IMP will be prepared according to the allocation by a Chinese medicine pharmacist. In the study, the registered CMP investigators, study subjects and outcome assessors will be kept blind of the allocated intervention.

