#### Statistical analysis

Basic demographic data (gender, age, *etc.*) will be descriptively summarized. Continuous variables are presented as mean ± standard deviation (SD) and categorical variables are presented as ratios. Intra group comparisons between baseline and each visit will be conducted by using paired *t*-test (or Wilcoxon signed rank test). Linear mixed model will be used to compare the outcomes between groups. All statistical tests will be two-sided, and *p* < 0.05 is considered significant difference. The statistical analysis will be done by an independent statistician and all analysis will be conducted by SPSS. If there is a significant difference in the use of western medicines between the treatment and control groups, it will be considered and processed as a covariance in the statistical analysis.

In this study, the subject will be deemed as “per protocol” if they have taken the maximum dose or if they stop until getting negative RAT results on two successive days and the major symptoms subside (defined as oral temperature ≤37.2°C, the score of cough and fatigue ≤1) with ≥85% intake compliance. The intake compliance is calculated by dividing the no. of packs of drugs ingested by either:a) the number of packs of core formula the subject should take daily (daily dose) x the number of days from the day of starting drug intake to the day the drug is stopped according to the criteria (e.g., if the subject should take 4 packs of core formula a day, starts taking drug on 1 January, stops at 8 January according to criteria, and has taken 30 packs, the compliance will be (30/(4 × 8)) x 100%) = 93.75%, with the subject deemed as “per protocol”; orb) daily dose x 14 for all other cases (e.g., if the subject should take 4 packs of core formula a day, starts taking drug in 1 January and stops at 3 January because of adverse events, and has taken 12 packs, the compliance will be (12/(4 × 14)) x 100%) = 21.43%, with subject deemed as not “per protocol”.

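### Randomisation is stratified by age group and vaccination, but the adjustment stated for the between-group linear model does not include these two factors; they should be named as fixed effects.

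*Protocol article*

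**What the plan says.** - **Design.** The section on baseline randomisation states "Specifically, the stratified randomisation is based on age" (18–49 and 50–65 years) and on number of vaccine doses (three or more; two or fewer). It adds: "Four subgroups will be created after stratification and subjects in each subgroup will be randomly assigned to either the treatment or placebo group". The allocation ratio is 1:1. The stated purpose is balance: "The distribution of age and number of vaccinations between the two groups will be roughly comparable after stratified randomisation".
- **Planned stratum size.** The sample size section plans 48 per arm, made up of 12 in each of the four strata (4 × 12 = 48).
- **Allocation list.** The section on randomisation and blinding says "A random number table will be generated with a computerized random number generator program". It mentions neither blocks nor another device that would enforce balance within a stratum.
- **Analysis.** The statistical analysis section says "Linear mixed model will be used to compare the outcomes between groups" and lists no model terms. It gives one adjustment rule, which begins "If there is a significant difference in the use of western medicines between the treatment and control groups"; in that case western-medicine use is to be handled as a covariate. Age group and vaccination group are not mentioned there.

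**The concern.** Stratified allocation that balances the arms within strata removes the strata's contribution from the true variance of the arm difference. A linear model without the strata still counts that contribution as residual noise. If the factors are prognostic, its standard error is then larger than the design warrants: confidence intervals are too wide, the test rejects less often than its nominal 5% under the null, and some of the precision that stratifying should bring is not used.

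The article's adjustment rule makes this more than a missing detail. The one candidate it names is measured after randomisation and enters only after a significance test, while the two baseline factors on which the trial randomises do not appear. A statistician who fitted the model from this text would ignore the design. Leaving the point open also allows a choice between adjusted and unadjusted results after the data are seen.

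**Working it through.** **Inputs from the protocol article**
- Difference: "the time to fever resolution of half a day (0.5 days) would have clinical significance".
- Standard deviation: "we assumed the standard deviation (SD) is 0.7" (taken as days).
- 80% power, two-sided 5%, 38 evaluable per arm, 20% dropout, 96 in total.

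**Assumed input.** R², the share of outcome variance explained by the strata, is not given in the documents. It is set to 0, 0.05, 0.10 and 0.20.

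**The plan's own figure.** n per arm = 2(1.960 + 0.842)² × 0.7² / 0.5² = 30.8, so 31 (32 with the t-test). The stated 38 is not reproduced. The next step is: 38/0.8 = 47.5, so 48 per arm and 96 in total. The gap between 38 and 31–32 is a separate matter and neither supports nor weakens this point. It does mean that power must be shown from two starting points: the nominal 80%, and the power that 38 per arm gives on the stated inputs. For the latter, 0.5 / (0.7 × √(2/38)) = 3.113, and Φ(3.113 − 1.960) = 87.6%.

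**Formulas, for balance within strata and a linear model.** Let k = √(1 − R²), and let λ be the difference divided by the unadjusted standard error (2.802 for nominal 80%; 3.113 for the stated inputs).
- Unadjusted standard error relative to the true one: 1/k
- Type I error of the unadjusted test: 2[1 − Φ(1.960/k)]
- Power, unadjusted: Φ((λ − 1.960)/k)
- Power, adjusted: Φ(λ/k − 1.960)

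Unadjusted power also rises with R², because the true variance of the difference falls while the test still uses the larger standard error. The gain from adjustment is therefore the difference between the last two lines, not the distance from 80%.

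| R² | SE factor | Type I error, unadjusted | Power from nominal 80%: unadjusted → adjusted | Power on stated inputs, 38 per arm: unadjusted → adjusted |
|---|---|---|---|---|
| 0 | 1.00 | 5.0% | 80.0 → 80.0% | 87.6 → 87.6% |
| 0.05 | 1.03 | 4.4% | 80.6 → 82.0% | 88.2 → 89.2% |
| 0.10 | 1.05 | 3.9% | 81.2 → 84.0% | 88.8 → 90.7% |
| 0.20 | 1.12 | 2.8% | 82.7 → 88.0% | 90.1 → 93.6% |

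Example at R² = 0.10: k = 0.949; 1.960/0.949 = 2.066, giving 3.9%; 0.842/0.949 = 0.887, giving 81.2%; 2.802/0.949 − 1.960 = 0.993, giving 84.0%.

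**Simulation** (10,000 trials per scenario, 40 per arm, four equal strata, difference 0.5, SD 0.7, adjustment by stratum indicators).
- *Balanced within strata.* At R² = 0.05, 0.10 and 0.20 the unadjusted type I error is 4.4%, 4.0% and 2.8%, against 4.9%, 4.9% and 5.0% adjusted. Power goes from 88.6 to 89.5%, 89.1 to 91.0% and 90.7 to 94.4%. At R² = 0 it is 88.5% against 88.4%.
- *Simple allocation, no balancing.* The unadjusted type I error stays near 5% (4.8%, 5.3%, 5.0%). Power goes from 88.0 to 88.2%, 88.0 to 89.7% and 87.5 to 92.7%. At R² = 0 adjustment costs a little, 88.3 to 86.8%. This run spends three degrees of freedom on strata, against two for main effects.

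**The case against.** **Silence is not exclusion.** A reader might infer that the plan leaves both factors out. The text does not support that: no model terms are listed, nothing rules the strata out, and an article commonly leaves the term list to a full protocol or analysis plan, which is not shown. The western-medicine sentence can be read as a contingency for concomitant drugs, a concern that the Discussion raises, and not as a closed covariate list. This stands. What remains is that the article does state an adjustment rule, and that the rule names a post-randomisation variable and neither design factor.

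**Excess standard errors are not established.** They require factors that predict the outcome and balance enforced within strata. No R² is given and no blocks are mentioned. The planned 12 per stratum per arm suggests that balance is intended, but gives no mechanism. With simple allocation the unadjusted test keeps its 5% level. This also stands, so the statement has to be conditional. The recommendation is less sensitive: in the simulation adjustment gained power under both forms of allocation once the strata explained some of the variance, though at R² = 0.05 with simple allocation the gain was negligible.

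**Not every comparison is affected alike.** It is tempting to extend the point to all secondary outcomes. The √(1 − R²) argument belongs to the linear model. In logistic regression, adjustment changes the odds ratio being estimated and does not shrink its standard error, and with rare events such as death or progression extra terms can make estimates unstable.

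**The error is on the safe side.** There is no inflation of false positives. That limits the point's weight but does not remove the case for a one-sentence correction.

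**Conclusion.** The point holds in conditional form. The article randomises by age group and vaccination, and the adjustment that it states for the linear mixed model does not include them. If the factors are prognostic, a model without them is less precise than it could be; if allocation is also balanced within strata, its standard errors are too large and its tests conservative.

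With balanced strata and an assumed R² of 0.05, 0.10 or 0.20, adjustment adds about 1, 3 or 5 points to a nominal 80% power. On the stated SD of 0.7 with 38 per arm, where power is already about 88%, it adds about 1, 2 or 4 points (1.0, 1.9 and 3.5 by formula; 0.9, 1.9 and 3.7 in the simulation with 40 per arm). At R² = 0 there is no gain. The documents support no particular value of R², so the unconditional reading, that power is being lost, goes further than they allow. This is a modest improvement in precision and in matching analysis to design; it is not a threat to validity.

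**What to change.** Add to the statistical analysis section, for example: *The between-group linear models for the primary outcome and the other continuous outcomes include age group (18–49, 50–65 years) and vaccination group (≥3, ≤2 doses), as used at randomisation, as fixed main effects. Any time-to-event model is stratified by or adjusted for the same two factors.*

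Rare binary outcomes such as mortality and progression to severe or critical illness need not be adjusted. If a fuller analysis plan already contains these terms, the article's text only has to be aligned with it.

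The cost is one sentence and two degrees of freedom (96 subjects less two arm means leaves 94). Both factors are known for every subject at randomisation, so no new data are needed. If the factors explain nothing, nothing is gained, and without balance within strata a small amount of power may be given up.

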### Study outcomes

#### Assessment

1. The time between starting medication and body temperature returning to normal and the recurrence rate of fever after momentary recovery. Each subject will be issued with the same type of oral thermometer for measurement at 9 a.m. (±2 h) and 9 p.m. (±2 h) daily, with at least 12 h between each measurement. Normal oral temperature is defined as equal to or below 37.2°C. Temperature recovery time is defined as the total number of days between medication starting date and the date of “normal oral temperature for 24 h without antipyretic” (both days inclusive). Subjects are required to measure the temperature until day 14 or on the day when the temperature has remained normal for 24 h, whichever is later.2. The negative rate of RATs at day 14 and negative conversion time. Each subject will be issued with the same type of RAT kits which can be used for at least 14 days for testing at 9 a.m. (±2 h) each day, with at least 24 h between each test. Negative conversion time is defined as the total number of days between the medication starting date and the date of securing two successive negative RAT results (both days inclusive). Subjects were required to undergo testing until day 14 or the day when two successive negative RAT results at least 24 h apart are obtained, whichever is later.3. The remission rate at day 14 and remission time of major symptoms.4. The disappearance rates at day 14 and disappearance time of symptoms. Subjects are required to record the status of their symptoms including major clinical symptoms daily at 9 p.m. (±2 h). Except for fever which is marked as ‘No’ or ‘Yes’ according to whether the oral temperature exceeds 37.2°C, other symptoms will be graded on a scale of 0–4 from “None”, “Mild”, “Moderate”, “Severe” and “Very Severe” depending on the actual feelings of the subject (“None” means the symptom is not present, “Mild” means the symptom is present but does not interfere with daily activities; “Moderate” means the symptom is present and slightly interferes with daily activities; “Severe” means the symptom is present and most daily activities cannot be done; “Very Severe” means the symptom is present and interferes with all daily activities). Major clinical symptoms include fever, cough and fatigue. Remission is defined as oral temperature ≤37.2°C, cough and fatigue score ≤1; disappearance is defined as the symptom being present at day 0 (score >0) but the symptom score is 0 at the date of recording.5. All-cause mortality at the 21st day after stopping the medication.6. Incidence of the progression to severe or critical illness during the trial. The all-cause mortality at the 21st day after stopping the medication and the incidence of the progression to severe or critical illness during the trial will be confirmed by communication with the subjects and/or other related person(s) or checking their medical record in the Hospital Authority. The definitions of severe and critical illness are based on the related definitions of “Coronavirus disease 2019 (COVID-19) Treatment Guidelines” published by National Institutes of Health (severe illness: oxygen saturation in the indoor environment of sea level <94%, oxygenation index [PaO2/FiO2] < 300 mmHg, respiratory frequency >30 breaths/min, lung infiltrates >50%; critical illness: respiratory failure, septic shock, and/or multiorgan dysfunction or failure).7. Utilization rates of antipyretic, Paxlovid and molnupiravir within 14 days and the total dosage(s) of the drug(s) used. In this study, subjects are allowed to take western medicines prescribed for the treatment of COVID-19 under the current guidelines of the Hong Kong Hospital Authority with at least 2 h’ gap between Chinese and western medicines. If oral temperature >39.0°C and continues over 4 h; or the oral temperature >39.5°C, the patient is advised to take antipyretic (paracetamol is recommended as a priority) for acute treatment. Patients need to record the amount and time of the drug(s) used.8. Oxygen saturation. For safety reasons, each subject will be issued with the same type of pulse oximeter for measurement at 9 a.m. (±2 h) and 9 p.m. (±2 h) daily, or whenever the subject decides it is necessary. If the reading is less than 94%, the patient is considered to have severe illness and has reached the end point of the study and is recommended to seek medical attention immediately. Subjects are required to measure their oxygen saturation at rest until day 14 or the time of body temperature returning to normal (continuing for 24 h) or the negative conversion time (2 successive negative RAT results), whichever is later.

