### Secondary outcomes

1. The recurrence rate of fever after momentary recovery: the incidence of fever recurrence (oral temperature > 37.2°C) within 24 hours after the patient’s temperature has normalized after treatment;2. The negative rate of RATs at day 14 and the negative conversion time (two successive negative RATs result with at least 24 hours interval);3. The remission rate of major symptoms at day 14 (oral temperature ≤ 37.2°C, score of cough and fatigue ≤ 1 (“None”, “Mild”, “Moderate”, “Severe” and “Very severe” were marked as 0 to 4 450 respectively), and continues 24 hours);4. Time of major symptoms remission: time from the start of treatment to symptoms remission (definition of symptoms remission: oral temperature ≤ 37.2°C, cough and fatigue score ≤ 1 and lasting at least 24 hours);5. The disappearance rates at day 14 and disappearance time of symptoms: the disappearance rates and time of individual symptoms of mild and moderate COVID-19 within 14 days (time defined as the period between starting medication and symptom disappearance); 6. The rate of patients whose oxygen saturation had gone below< 94% after intake of drugIMP, measured at day 14;7. Incidence of the progression to severe or critical illness during the trial;8. All-cause mortality at the 21st day after stopping the medication;9. Utilization rates of antipyretic, Paxlovid and molnupiravir within 14 days and the total dosage(s) of the drug(s) used.

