As telemedicine is the primary consultation method for this study, subjects will not visit the clinic throughout the study period and all communication with subjects will be via internet and delivery service. There is a risk of privacy breaches if documents are lost. Therefore, the postal documents in this study will only be marked with a code and abbreviation, and personal details will be filled in for the identification purposes after they are returned.

Since the use of other medications for COVID-19 is not prohibited in this study, the results of the study may be influenced by other medications taken by the subjects rather than this study medication. For this reason, the amount and using time of other medication must be recorded and become an important outcome for statistics, so that we could have a more accurate result of the effect of Yinqiao Powder-Maxing Ganshi Decoction.

We are aware that shedding of dead virus might still occur after patients have recovered from all major symptoms. However, we still think including the negative rate of RATs at day 14 and negative conversion time as secondary outcomes are valuable, for according to one study which investigated 14 different brands of RATs, RATs have very high specificity (100%) for all Ct values, and high sensitivity (88.18%) when Ct value is at or below 30, a threshold above which no virus can be cultured according to another study (Young et al., 2020; Routsias et al., 2021). Their sensitivity lowers to 37.5% when Ct values are from 31 to 35 (Routsias et al., 2021). This suggests RAT positivity is highly correlated with infectiousness, in sharp contrast to PCR tests, which detect non-infectious viral materials for an extended period post infection (Widders et al., 2020). Such properties of RATs have lead a New Zealand expert to deem RATs as the ideal option for “test-to-release” schemes to be adopted by governments for infection control (Science Media Centre, 2022). In fact, the Hong Kong and United Kingdom governments have adopted such schemes during the pandemic (GOV.UK, 2022; Information Services Department, 2022).

In this study, we will distribute RAT kits to subjects for their use and no PCR test will be conducted in the study period. Therefore, we think the rate of false positive by detecting dead virus can be minimized, and these outcomes will be of interest to policymakers and public health researchers.

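### Western-medicine use enters the model whenever it differs significantly between arms, with no restriction to use before randomisation; for antipyretics this adjusts for a consequence of the fever being measured

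*Protocol article*

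**What the plan says.** The rule stands in the Statistical analysis section: "If there is a significant difference in the use of western medicines between the treatment and control groups, it will be considered". The rest of that sentence has the variable enter the analysis under the term covariance, which I read as covariate. The same section fixes the model ("Linear mixed model will be used to compare the outcomes between groups") and the tests ("All statistical tests will be two-sided", with significance at p < 0.05). The rule names no outcome, sets no time window for the drug use, and does not say whether the adjusted model replaces the unadjusted one.

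Other sections show that use during the trial is meant, at least in part:

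- Assessment, item 7: above stated temperature thresholds (over 39.0°C for more than 4 h, or over 39.5°C), "the patient is advised to take antipyretic (paracetamol is recommended as a priority) for acute treatment". Amounts and times are recorded.
- Secondary outcomes, item 9: "Utilization rates of antipyretic, Paxlovid and molnupiravir within 14 days and the total dosage(s) of the drug(s) used".
- Discussion: because other drugs are permitted, "the amount and using time of other medication must be recorded and become an important outcome for statistics", with the aim of measuring the study drug's effect more accurately.

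The primary outcome is the time from starting medication to normal temperature. Assessment, item 1, requires that the 24 hours of normal temperature be free of antipyretic. The Primary outcome section does not repeat that condition.

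**The concern.** Antipyretic use after randomisation lies downstream of the fever that the primary outcome measures. Subjects whose fever is higher or longer have more reason to take it, and a treatment that shortens fever can reduce it. A model that compares the arms at equal antipyretic use no longer estimates the whole effect of assignment, and randomisation no longer protects the comparison.

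The significance trigger adds a second problem. Without a significant difference in use, the analysis estimates the total effect. With one, it estimates an effect conditional on later drug use. The condition is more likely to be met when the treatment has lowered use. The target of estimation therefore depends on the data, and the adjustment tends to act against an effective treatment.

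**Working it through.** **Inputs from the article.** SD 0.7 day; difference 0.5 day; 38 per group before dropout; 80% power; two-sided 5% (Sample size estimation and Statistical analysis). **Assumed, because the article gives no figure:** how common antipyretic use is, and how strongly it depends on fever duration.

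**1. The plan's own figure.** The plan states "38 in each group will be needed with a power of 80% and a 5% 2-tail significance level". The usual formula gives n = 2 × (1.96 + 0.84)² × 0.7² / 0.5² ≈ 30.8, so 31 per group, or 32 with the exact t-test. The stated 38 is not reproduced. The next step is: 38 / 0.8 = 47.5, so 48 per group and 96 in total. The gap between 31 and 38 is a separate matter and does not affect this point. With 38 per arm the standard error is 0.7 × √(2/38) = 0.161, and 0.5 / 0.161 ≈ 3.11. Power is Φ(3.11 − 1.96) ≈ 0.876, or 0.867 by t-test. That is the unadjusted benchmark of about 87%.

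**2. What adjustment does in principle.** Let fever duration be Y, with a treatment difference of 0.50. Let the amount of antipyretic depend linearly on Y, with within-arm correlation r and no other effect of treatment on use. The adjusted treatment coefficient is then 0.50 × (1 − r²):

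- r = 0.3: 0.50 × 0.91 = 0.455
- r = 0.5: 0.50 × 0.75 = 0.375
- r = 0.7: 0.50 × 0.51 = 0.255

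The attenuation follows algebraically from adjusting for a consequence of the outcome.

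**3. The rule as written, with amount of use as the covariate.** Simulation with 4,000 trials per setting; the covariate is added only if use differs at p < 0.05.

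| r | Rule fires | Mean reported effect (day) | Power |
|---|---|---|---|
| 0 | 5% | 0.51 | 87.5% |
| 0.3 | 15% | 0.48 | 84% |
| 0.5 | 34% | 0.43 | 79% |
| 0.7 | 59% | 0.31 | 62% |

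**4. The rule as written, with use as yes/no.** Fever duration is 2.5 − 0.5 × arm + N(0, 0.7). The probability of use is logistic in duration with slope k. The drug taken has no effect on fever. A chi-square test decides whether use enters the model. Where two values are shown, they come from repeated runs.

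| Setting | Rule fires | Mean reported effect (day) | Power | 95% interval covers 0.50 |
|---|---|---|---|---|
| k = 1.5 | 25–27% | 0.45–0.46 | 81–82% | 94% |
| k = 3 (use 61% v 39%) | 47–49% | 0.37 | 70–71% | 84% |
| k = 5 | 60–61% | 0.30–0.31 | 59–60% | 65% |
| k = 3, rarer use (20% v 9%) | 32% | 0.43 | 78% | – |
| k = 1.5, rarer use (29% v 17%) | – | 0.47 | 84% | – |

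Runs differ by a percentage point or so.

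**5. No treatment effect.** In both models the type I error under the rule stayed at about 0.03 to 0.05.

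**The case against.** **The size is assumed.** This stands. The antipyretic advice is tied to a temperature peak, while the simulations tie use to duration. Entry needs only a temperature above 37.2°C, and the article does not say how many subjects would reach the advice thresholds. Subjects may also take antipyretics at lower temperatures on their own initiative. If use is uncommon or weakly related to duration, the loss is small.

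**Stronger readings.** A reader might infer that the adjustment removes the effect, that it acts exactly when the treatment works, or that it invalidates the p-value. The working does not support these. In the strongest yes/no scenario the fully adjusted effect is still 0.24 of 0.50 day. The rule fires in about 25% to 61% of the yes/no trials with a real effect, not in all of them. With no effect, the test keeps its level.

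**Scope.** Western medicines include antivirals as well. The introduction describes local antiviral use as directed mainly at people aged 60 or over and at high-risk or chronically ill patients, many of whom the eligibility criteria exclude. The simulations do not cover antivirals, and the bias there could go either way. Treatment already under way at entry may continue, and adjusting for use begun before randomisation is legitimate.

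**Status of the sentence.** It does not say that the adjusted model replaces the unadjusted one, and a fuller protocol or analysis plan may settle this. But the article states a positive rule with no limit on timing or role, and the Discussion gives accuracy of the effect estimate as the reason for recording other drugs. Read plainly, the rule reaches the primary analysis.

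**Conclusion.** The point holds for antipyretics taken after randomisation. The article makes adjustment depend on a between-arm test of a variable that treatment can change, that responds to the measured fever, and that is a secondary outcome in its own right. When the treatment works, the expected result is an estimate that is too small, reduced power, and intervals that cover the true effect less often than 95%. An excess of false positives is not expected.

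Across the yes/no settings, a true 0.50-day effect is reported on average as about 0.47 down to 0.30 day. Power is about 83% down to 59%, against about 87% without adjustment. At the mild end the trial still reaches its planned 80%; with moderate to strong dependence and common use it does not. These figures assume that the adjusted result replaces the unadjusted one, that use depends on fever duration, and that the drug taken does not itself shorten the measured fever. For antivirals begun after randomisation, the adjusted comparison is equally unprotected by randomisation, but the direction of bias cannot be stated.

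**What to change.** Replace the conditional sentence in the Statistical analysis section with four statements:

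1. The primary analysis does not adjust for any medication taken after randomisation.
2. If adjustment for western medicine is wanted, it uses only use recorded at screening, is fixed in advance, and does not depend on a between-arm test.
3. Use during the trial is reported by arm, as the secondary outcome it already is.
4. Any analysis that adjusts for use during the trial is labelled a sensitivity analysis and does not replace the primary result.

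Also reconcile the Primary outcome section with Assessment, item 1, on whether the 24 hours of normal temperature must be free of antipyretic, so that antipyretic use is handled within the endpoint. The description of the estimand should then say so: antipyretic use is part of the endpoint definition, and other later medication is disregarded under a treatment-policy approach.

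The cost is a few sentences in two sections. Table 1 already schedules concomitant medication at screening, and use during the trial is already recorded. No new data are needed and no clinical rule changes.
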